## Abstract

**Background:**

Nutrition transition in developing countries were induced by rapid changes in food patterns and nutrient intake when populations adopt modern lifestyles during economic and social development, urbanization and acculturation. Consequently, these countries suffer from the double burden of malnutrition, consisting of unresolved undernutrition and the rise of overweight/obesity. The prevalence of the double burden of malnutrition tends to be highest for moderate levels (third quintile) of socioeconomic status. Evidence suggests that modifiable factors such as intra-household food distribution and dietary diversity are associated with the double burden of malnutrition, given household food security. This article describes the study protocol of a behaviorally based nutrition education intervention for overweight/obese mothers with stunted children (NEO-MOM) in reducing the double burden of malnutrition.

**Methods:**

NEO-MOM is a randomized controlled trial with a three-month behavioral intervention for households involving pairs of 72 stunted children aged 2–5 years old and overweight/obese mothers (SCOWT) in urban Indonesia. The SCOWT pairs were randomly assigned to either an intervention group or to a comparison group that received usual care plus printed educational materials. The intervention consisted of six classroom sessions on nutrition education and home visits performed by trained community health workers using a motivational interviewing approach. The primary outcomes of this study are the prevalence of double burden of malnutrition as measured in SCOWT, child’s height-for-age z-score (HAZ) and maternal body mass index (BMI).

**Discussion:**

Because previous studies are mainly observational in nature, this study advances understanding of the double burden of malnutrition through a fully powered randomized controlled trial. The intervention assists participants in self-administered goal setting to improve diet and child feeding behaviors by improving self-efficacy. Maternal self-efficacy may be enhanced through vicarious and active mastery of experiences gained during six sessions of nutrition education and verbal persuasion during home visits.

**Trial registration:**

The Universal Trial Number (UTN) for this study is U1111-1175-5834. This trial was registered in the Australian New Zealand Clinical Trials Registry (ANZCTR) and is allocated the registration number: ACTRN12615001243505 on 12 November 2015.

## Background

### Double burden of malnutrition

Children of the world still suffer from malnutrition, and more than 25 % of under-five children in developing countries are stunted [1]. Stunted children do not grow well, and they are shorter in stature than normal children of their age. Childhood stunting is associated with suboptimal brain development, which leads to impaired cognitive ability and school performance, and reduces earning potential later in life [2]. Acknowledging the detrimental consequences of child stunting, the World Health Organization (WHO) and its member countries have pledged to achieve a 40 % reduction by 2025 through the Scaling up Nutrition (SUN) program [2].

While the battle with stunting is far from over, developing countries have been hampered by another nutrition problem. In the mid-1990s, Popkin [3] observed that the phenomenon of coexistence between overweight and obesity and undernutrition mostly occurred in developing countries. Since then, the double burden of malnutrition has raised public health concerns regarding its consequences. First, there is, concern that the burden of disease may increase as a result of vitamin, mineral and protein deficiencies brought about by undernutrition. Overnutrition increases the risk of noncommunicable diseases (NCD), including obesity, hypertension, type 2 diabetes, and cardiovascular diseases. The presence of NCDs accounted for 80 % of the total disease mortality burden in developing countries, with an estimated $84 billion of economic production lost due to heart disease, stroke, and diabetes alone [4]. Hence, the presence of double burden of malnutrition poses an additional burden on the already inadequate and overextended health budget in developing countries [5].

Most developing countries experience nutrition transition, or rapid changes in dietary patterns and nutrient intakes, when populations adopt modern lifestyles during economic and social development, urbanization and acculturation [3]. Popkin [6] argued that the double burden of malnutrition in one household is related to urbanization. With urbanization, household incomes increase and food becomes more available in terms of quantity, but not quality [7]. Available food is high in energy, but low in micronutrients and protein that affect child growth, especially height. Receiving insufficient micronutrients and protein in the first two years of life, increases the child’s risk of being stunted [2]. Mothers that consume high energy food accompanied by low physical activity, are at increased risk of overweight and obesity. Indonesia, the fourth most populous country in the world, has suffered from the double burden of malnutrition. The prevalence of child stunting in Indonesia was 36.8, 35.6 and 37.2 % in 2007, 2010 and 2013, respectively [8], while the prevalence of obesity (based on Asian cut-off BMI > 27) among women (aged > 18 years old) has continued to increase. In 2007 the obesity prevalence among women was only 13.9 %; in 2010 it was 15.5 % and in 2013 it was 32.9 % [8]. Some have suggested that East Java Province is a microcosm of Indonesia in terms of achievement in child health outcomes in Indonesia. The prevalence of child stunting in East Java was similar to the national figure of around 35 % [8]. A study in rural Indonesia showed that the prevalence of the coexistence of child undernutrition that includes stunting and maternal overweight/obesity (SCOWT) was 11 % [9].

Evidence shows that food insecurity is one of the risk factors for child stunting, but there is currently little evidence that food insecurity is risk factor for double burden of malnutrition [10]. A cross sectional study in rural Indonesia demonstrated that higher intakes of animal products was protective against SCOWT [11], but the lack of animal protein intake was more indicative of dietary diversity than a valid indicator for food insecurity. A previous study revealed the double burden of malnutrition to be most prevalent, at 22.7 %, among the middle (third) quintile of socioeconomic status (SES) in a Guatemalan population [10]. This evidence suggests that at the household level, in the absence of food insecurity and economic deprivation, modifiable factors such as food distribution and dietary diversity were associated with the high prevalence of double burden of malnutrition in this third quintile group, relative to the others. We hypothesize that stunted children in households that suffer from the double burden of malnutrition are less likely to be facing food insecurity. Evidence showed that strategies to reduce overweight and obesity should emphasize recommending increased fruit and vegetable consumption with explicitly combining this approach with other efforts [12] such as increasing physical activity [13].

We aim to target the modifiable behaviors related to the double burden of malnutrition in an urban setting in Indonesia through an intervention offering nutrition education for overweight/obese mothers with stunted children (NEO-MOM). This article describes the rationale and methods for the randomized controlled trial conducted in urban Indonesia to reduce the prevalence of double burden of malnutrition as measured in SCOWT pairs.

## Methods/Design

This RCT was a superiority trial consisting of 2-arm parallel groups (an intervention group and a comparison group that received usual care along with printed educational materials). A three-month behavioral intervention was delivered to the two groups made up of households with stunted children aged 2 to 5 years and overweight/obese mother (SCOWT pairs). After an initial screening procedure, the 72 women with stunted children who consented to participate were randomly assigned to either the intervention or comparison group. The study employed parallel assignment with the two groups of participants receiving different interventions during the same time span. The two groups — the enhanced behavior change intervention group (NEO-MOM) and a comparison group receiving printed materials (PRINT) — were each made up of 36 overweight/obese mothers with a stunted child. Baseline data was gathered from participants in their homes at the beginning of the study. Another visit to collect post-intervention data followed the three-month intervention. The adapted CONSORT diagram in Fig. 1 shows progression through the study for individual participants.

**Fig. 1 Fig1:**
[figure not shown]
Adapted CONSORT diagram of the study

### Objective and hypothesis

The objective of the RCT was to evaluate the effectiveness of a behaviorally based nutrition education (NEO-MOM) intervention in reducing the prevalence of household double burden of malnutrition as indicated by stunted child and overweight/obese mother (SCOWT) pairs.

#### Primary hypothesis

The NEO-MOM intervention, consisting of six sessions of behaviorally based nutrition education and home visits, will be more effective in reducing SCOWT prevalence in the intervention group, relative to the comparison group.

#### Secondary hypothesis

We hypothesized that after six sessions of behaviorally based nutrition education (NEO-MOM) accompanied by biweekly home visits, relative to the comparison group, mothers in the intervention group would:Show a greater increase in average maternal fruit and vegetables intake and average child animal protein intake.Show a greater increase in maternal self-efficacy for fruit and vegetable intake, as well as improved child-feeding behavior for protein intake.Show a greater increase in maternal physical activity (average number of steps per day assessed via pedometer).Show larger reductions in maternal sedentary time.

### Ethical approval

The Institutional Review Board (IRB) at Kansas State University approved the trial (reference or proposal number: 7894). The screening portion was also approved by the IRB at Kansas State University (reference or proposal number: 7646). In addition, this trial is approved by the Surabaya City Review Board (Bakesbangpol No: 1366/LIT/2015) in Indonesia. The main ethical consideration was to ensure that risk of harm to participants was minimized and that they were fully informed of any risk. Religious and cultural sensitivities were taken into account when obtaining informed consent. Recruitment and informed consent were handled so potential participants were not pressured to participate, and confidentiality was preserved. All participant data was stored using code system and electronic data remains password protected.

We obtained informed consent during monthly community health post meeting (*posyandu*), where mothers brought children under five years of age for growth monitoring. Research assistants invited potential participants to meet in a separate room, giving them verbal and written information about the study and at least one week to think about their participation. Participants were free to withdraw from the study at any time without negative consequences.

A copy of participant informed consent will remain on file for 12 months after the completion of the study. Personal data with participant identification will be destroyed after 3 years following completion with other records archived for five years before being destroyed. The Universal Trial Number (UTN) for this study is U1111-1175-5834. This trial is registered in the Australian New Zealand Clinical Trials Registry (ANZCTR) and is allocated the registration number: ACTRN12615001243505. The ANZCTR is recognized as an ICMJE (the International Committee of Medical Journal Editors) acceptable registry and a Primary Registry in the WHO registry network.

### Setting

The study is set in urban city of Surabaya, Indonesia. Surabaya is the second largest city in Indonesia with more than 3.1 million inhabitants and 5.6 million in the metropolitan area [14]. Popkin [3] has argued that urbanization is one of the driving forces for the double burden of malnutrition, and that Surabaya is a prime setting for studying the phenomenon of nutrition transition and the double burden of malnutrition. Surabaya has a big port and industries that make it a melting pot for urbanization from the eastern part of Indonesia. Surabaya was chosen as the setting of this study because it spans the range of population densities, urbanization, and socioeconomic profiles. Because Indonesia is an archipelago country, recruiting participants from every major city on each island would have been cost prohibitive. A limitation, however, is that Surabaya may not be representative of urban cities in Indonesia and may not address health and nutrition inequalities across islands. Many health and nutrition inequalities exist within Surabaya City that mirror other urban settings in Indonesia [15].

### Target population

The sample was drawn from community health posts *(“posyandu”)* [16] listing more than 50 mothers with children under the age of five. Informed consent was gathered from all participants before undergoing screening to validate their eligibility for participation. The case definition included overweight/obese mothers (BMI > 25) with stunted children (HAZ < -2). A BMI cut-off point of >25 kg/m2 was used to determine maternal overweight and obesity, while child stunting was defined as HAZ < -2, according to the child growth standard from the WHO-Anthro 2005. Repeated anthropometric measurement for both mothers and children are performed by trained research assistance in *posyandu*. A third measurement was initiated when the discrepancy between the first and the second measurement was greater than 1 %. An average of anthropometric measurements was used to determine eligibility. Following screening via anthropometric measurement, those eligible were invited to participate in the study.

### Inclusion and exclusion criteria

Inclusion criteria required participants to be fluent in conventional Bahasa Indonesia language, a permanent resident planning to stay in Surabaya City for at least six months, the mother of a stunted child under age five, and overweight/obese. In addition, the child had to be registered in *posyandu* and receiving food supplementation from the government. Participants were excluded in cases where either the mother or the child had physical disability, mother was participating in a weight loss program or deliberately fasting due to a spiritual deed; mother was pregnant; or the child had been diagnosed with serious medical problems.

### Power calculation

The power calculation of the main outcome variable was based on a previous RCT in Bangladesh that explored effects of a similar three-month nutrition education intervention with complementary feeding on child’s height gain [17, 18]. Although the study did not directly provide complementary feeding, one of the inclusion criteria was that participants would be eligible to take part in a complementary feeding program administered by the government of Indonesia. The effect size of providing complementary food and intensive nutrition education on height gain (cm) in Bangladesh was 0.80 (95 % CI = 0.007–1.53). We selected this fairly large effect size of 0.8 expressed as mean difference in child height, which translates to an ability to detect a difference between two groups of 0.80 cm in child height at a three-month follow-up. The study has a 90 % power to detect modest changes at the individual level that would have an important impact if occurring at the population level. A minimum total sample size of 66 was needed to detect these differences in our primary hypothesis, with two-tailed alpha of 0.05. Assuming a dropout rate of 9 %, the total sample size of 72 was required (36 in the intervention group and 36 in the comparison group/usual care).

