### Comparison group: usual care plus print educational materials

The comparison group did not receive nutrition education or home visits by a community health worker. Participants in the comparison group received sets of printed educational materials, coupled with benefits from a government food supplementation program. The sets of printed educational materials (booklets) were provided after baseline data measurement for both intervention and comparison group. Printed material was chosen as the medium for source of information due to several considerations: to mimic government strategy for distributing the health messages through the “Kartu Menuju Sehat” (KMS) or a child’s growth monitoring card and because it was deemed unethical not to provide anything for participants knowing they had double burden of malnutrition in the form of SCOWT. Finally, these materials were provided to minimize the threat to internal validity that might occur. By providing the comparison group with the same printed educational materials, we aimed to avoid resentful demoralization of participants in the comparison group. All mothers participating in the study received usual care in the form of monthly growth monitoring of their child’s nutritional status at *posyandu* and access to a supplementary feeding program from Indonesian government. Supplementary feeding program was given for children under 5 years old that consist of foods equivalent with 1000 to 1550 kcal total energy and 25–39 g protein [22].

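### The 90% power for a 0.80 cm difference rests on an unstated SD of 1.0 cm and on an effect borrowed from a different contrast, so it is unsupported

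*Protocol article*

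**What the plan says.** All places are in the protocol article.

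- **Power calculation**, source of the effect: "The effect size of providing complementary food and intensive nutrition education on height gain (cm) in Bangladesh was 0.80", with a 95% CI of 0.007 to 1.53.
- **Power calculation**, how it is used: "We selected this fairly large effect size of 0.8 expressed as mean difference in child height". The section says this translates to "an ability to detect a difference between two groups of 0.80 cm in child height at a three-month follow-up".
- **Power calculation**, error rates and size: "The study has a 90 % power to detect modest changes at the individual level" and "with two-tailed alpha of 0.05". The minimum total is 66, raised to 72 (36 per arm) for 9% dropout. No SD is given here or elsewhere in the article.
- **Primary outcome**: the outcome on which power was calculated is the change in the child's height in cm.
- **Inclusion and exclusion criteria**: the child must be "receiving food supplementation from the government".
- **Comparison group**: "Participants in the comparison group received sets of printed educational materials, coupled with benefits from a government food supplementation program".
- **Intervention** and its Table 1: both arms receive the booklets. The NEO-MOM arm also has six classes, six home visits and a grocery voucher at each class attended.
- **Abstract, Discussion**: the trial is described as fully powered.

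**The concern.** Two inputs to the power statement do not support it.

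**Units.** A difference in centimetres and an effect size in SD units are the same number only when the SD is 1.0 cm. The text treats them as the same without giving an SD. It also refers to height at follow-up, whereas the Primary outcome section says change in height; the two have different SDs, so the text should name one.

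**Contrast.** The 0.80 cm is attributed to food together with education. The Power calculation section uses the government feeding programme as the link to that trial. In this trial, however, the programme is an entry condition and reaches both arms, so it is not part of what is randomised. The plan gives no reason why the remaining contrast should yield the whole 0.80 cm.

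What is at stake is how a null result is read. If the trial is reported as having 90% power, a null result looks like evidence against an effect of 0.80 cm. If true power was nearer 50%, it says little. The section also claims power for modest changes directly after calling the design effect fairly large.

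**Working it through.** **Inputs from the Power calculation section:** two-sided alpha 0.05, power 90%, effect 0.8, 1:1 allocation, 66 before and 72 after 9% dropout. The SD is not given.

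**1. Reproduce the plan's figure.** The normal formula is n per arm = 2(z₀.₉₇₅ + z₀.₉₀)² / (δ/SD)². With δ/SD = 0.8:

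2 × (1.96 + 1.2816)² / 0.8² = 32.8, so 33 per arm and 66 in total, an exact match.

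The t-test version needs 34 per arm (68), and 33 per arm gives 89.3% power. For dropout, 66 × 1.09 = 71.9, which gives 72; 66 / 0.91 = 72.5 would give 73. That difference is immaterial.

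**2. Solve for the SD implied by 0.80 cm.** SD = 0.80 × √(33/2) / (1.96 + 1.2816) = 1.00 cm. The stated sample size therefore carries an SD of 1.0 cm that the text never mentions.

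**3. Power for 0.80 cm at other SDs** (two-sided t-test; SDs are assumptions):

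| SD of height change, cm | Standardised difference | Power, 33 per arm | Power, 36 per arm (no dropout) |
|---|---|---|---|
| 0.8 | 1.00 | 98% | 99% |
| 1.0 | 0.80 | 89% | 92% |
| 1.2 | 0.67 | 76% | 80% |
| 1.5 | 0.53 | 57% | 61% |
| 2.0 | 0.40 | 36% | 39% |

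By the normal formula, 90% power would need a total of 148 analysed at SD 1.5 and 264 at SD 2.0.

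**4. Smaller between-arm differences** (33 per arm; differences and SDs are assumptions):

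| Difference, cm | SD 1.0 | SD 1.5 | SD 2.0 |
|---|---|---|---|
| 0.8 | 89% | 57% | 36% |
| 0.6 | 67% | 36% | 23% |
| 0.4 | 36% | 19% | 13% |

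**5. What the quoted CI suggests (illustration only).** The full width gives SE = (1.53 − 0.007) / 3.92 = 0.39. The upper half-width gives 0.73 / 1.96 = 0.37. For a simple, unadjusted comparison of two equal arms of size m, SD = SE × √(m/2). An SD of 1.0 would then correspond to m of about 13 to 14. At m = 30 the SD is 1.4 to 1.5 cm, and at m = 60 it is 2.0 to 2.1 cm. The article gives neither the arm sizes nor the design of the source trial.

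**6. What differs between arms.**

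| Component | NEO-MOM | Comparison |
|---|---|---|
| Government food supplementation | yes | yes |
| Booklets | yes | yes |
| Vouchers at baseline and evaluation | yes | yes |
| Six classes | yes | no |
| Six home visits | yes | no |
| Voucher at each class attended | yes | no |

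The randomised contrast is the last three rows. The source effect is described as that of food and education together.

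**The case against.** The best defence is that the arithmetic is right: 66 reproduces exactly, and the SD of three-month height change may really be 1.0 cm. The Statistical analysis plan section includes an ANCOVA on changes adjusted for baseline, which could lower the relevant SD. With SD 1.0 cm and a true difference of 0.80 cm, power is 89 to 90%. All of this stands, and it limits the conclusion to a claim without support. It does not supply that support, because neither an SD nor a correlation is stated.

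Several stronger readings are tempting, and the document does not support them:

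- *The design delivers less than 90% power.* Not shown, because the SD is unknown.
- *Only education and visits differ between arms.* Incorrect. The session vouchers also differ, and Table 1 presents them as a means of increasing access to food.
- *0.80 cm is an upper bound for this trial.* Not shown. The source trial's comparator is not described, and this trial adds home visits and vouchers. The article also states openly that the study did not itself provide complementary feeding.
- *Power is close to nil because raw height varies by several centimetres among children of this age.* The Primary outcome section names change as the powered outcome, so powers for unadjusted follow-up height do not apply. The loose phrase about height at follow-up needs correcting and implies nothing more.
- *The quoted CI proves an SD above 1.0 cm.* It does not. The back-calculation assumes a simple two-arm, individually randomised design. In addition, the interval is not symmetric about 0.80 (its midpoint is 0.77), so it may contain a typing error.

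**Conclusion.** The concern holds as a failure of support. The sample size is correct for a standardised difference of 0.8. The claim of 90% power for 0.80 cm adds an SD of 1.0 cm that is neither stated nor sourced, and a between-arm effect taken from a package whose food component both arms receive here. Over assumed SDs of 1.0 to 2.0 cm, power for 0.80 cm with 33 per arm runs from 89% down to 36%. At SD 1.0 cm, a true difference of 0.4 cm would have 36%. These figures rest on a two-sided t-test at 0.05, 33 analysed per arm, and SDs and smaller differences that are assumptions. They show how strongly the claim depends on the missing inputs and do not estimate the trial's actual power. The 90% and fully powered statements should not stand as written, because they govern how a null result would be read.

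**What to change.** Keep 72 participants and change the power statement.

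1. Restate it, for example: *33 analysed per arm give about 89–90% power (two-sided 0.05) for a standardised difference of 0.8 in three-month change in height, that is 0.80 × SD cm.*
2. State the SD of three-month height change, or the baseline-adjusted residual SD, with its source. Failing that, show power over an assumed SD range of 1.0 to 2.0 cm and over between-arm differences of, say, 0.4 to 0.8 cm.
3. Replace the sentence that converts 0.8 into 0.80 cm, the reference to height at follow-up (name change in height, as the Primary outcome section does) and the reference to modest changes.
4. Say that the source effect includes food, that both arms receive government food and booklets here, that the randomised difference is classes, home visits and session vouchers, and that the source effect may therefore not carry over in full.
5. Qualify the description of the trial as fully powered. If an SD is back-calculated from the quoted CI, label it as illustrative.

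The cost is wording and a short table, with no change to design, sample size or analysis. The downside is that the stated power becomes less favourable.
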